## ***4.5. DESCRIPTION OF ASSESSMENT AND OF DATA COLLECTED***

### **4.5.1.Detailed description of evaluation parameters**

NPUAP scale:

This scale allows the evaluation of pressure sores according to 4 stages graduated from 1 to 4. Stage 1 being the least severe. The National Pressure Ulcer Advisory Panel's ([www.npuap.org](http://www.npuap.org)) Stages scale translated from English by ANAES will be used.

| stade |                                                                                   | description                                                                                                                                                                                                                                                                                                                                                                                                                                                                                                                                                                                                      |
|-------|-----------------------------------------------------------------------------------|------------------------------------------------------------------------------------------------------------------------------------------------------------------------------------------------------------------------------------------------------------------------------------------------------------------------------------------------------------------------------------------------------------------------------------------------------------------------------------------------------------------------------------------------------------------------------------------------------------------|
| I     | [figure not shown] | Le premier stade est une altération observable d'une peau intacte, liée à la pression et se manifestant par une modification d'une ou de plusieurs des caractéristiques suivantes en comparaison avec la zone corporelle adjacente ou controlatérale : température de la peau (chaleur ou froideur), consistance du tissu (ferme ou molle) et/ou sensibilité (douleur, démangeaisons). Chez les personnes à la peau claire, l'escarre apparaît comme une rougeur persistante localisée, alors que chez les personnes à la peau pigmentée, l'escarre peut être d'une teinte rouge, bleue ou violacée persistante. |
| II    | [figure not shown] | Perte d'une partie de l'épaisseur de la peau; cette perte touche l'épiderme, le derme ou les deux. L'escarre est superficielle et se présente cliniquement comme une abrasion, une phlyctène ou une ulcération peu profonde.                                                                                                                                                                                                                                                                                                                                                                                     |
| III   | [figure not shown] | Perte de toute l'épaisseur de la peau avec altération ou nécrose du tissu sous-cutané ; celle-ci peut s'étendre jusqu'au fascia, mais pas au-delà. L'escarre se présente cliniquement comme une ulcération profonde avec ou sans envahissement des tissus environnants.                                                                                                                                                                                                                                                                                                                                          |
| IV    | [figure not shown] | Perte de toute l'épaisseur de la peau avec destruction importante des tissus, ou atteinte des muscles, des os, ou des structures de soutien (par exemple des tendons, des articulations). Un envahissement et des fistules peuvent être associés au stade IV de l'escarre                                                                                                                                                                                                                                                                                                                                        |

#### ROMPIS scale:

To assess the intensity of mucosal injury, The Reaper Oral Mucosa Pressure Injury Scale (ROMPIS) will be used. First published in 2017 (9), the ROMPIS scale is the only scale to assess mucosal injury in this setting.

| Stage | Descriptor                                                                                                                                                                                                                                                                                               |
|-------|----------------------------------------------------------------------------------------------------------------------------------------------------------------------------------------------------------------------------------------------------------------------------------------------------------|
| 1     | Redness and demarcation of the lip and buccal mucosa, with no visible destruction or loss of epithelial tissue, ulceration or blisters. Non-blanchable erythema on the corners of the mouth.                                                                                                             |
| 2     | Destruction and differentiation of buccal mucosa, as manifested by blisters, soft coagulum, or clotting on mucosal tissue; superficial loss of non-keratinised epithelial tissue; or damage to epidermal and dermal layers of the corners of the mouth, without evidence of damage to underlying fascia. |
| 3     | Loss of mucosa and sub-mucosal tissue as evidenced by damage to/exposure of the fascia and underlying muscle in the lips or corners of the mouth.                                                                                                                                                        |

#### Adjudication Committee:

Several dermatologists and 2 nurses independent of the study will compose the adjudication committee. Each file (including all the photos of the same patient) will be randomly transmitted to each member of the adjudication committee. The members will rule on the presence or

absence of a lesion. If there is a discrepancy between the opinions of the committee members (if at least one of the experts disagrees with the other two), the committee will meet to discuss the matter and decide together whether or not the lesion is present.

#### **4.6. IDENTIFICATION OF ALL SOURCE DATA NOT INCLUDED IN THE MEDICAL RECORD**

Daily :

- Peri-oral lesions according to the NPUAP and ROMPIS scales
- Number of endotracheal tube mobilizations
- Presence or not of a protection of the ETT tube by specific system (guedel or mouthpiece)

Data related to photo adjudication: presence or absence of peri-oral lesions

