### **2.2.2. Secondary endpoint(s)**

- Number of self-extubations
- Number of significant repositioning of the endotracheal tube performed following a movement of more than 2 cm from the initially set marker.
- Time to the first peri-oral lesion from the time the patient is intubated until extubation.
- Assessment of the grade of cutaneous peri-oral lesions by the NPUAP scale.  
If several lesions co-exist, the lesion with the most severe grade will be retained.
- Evaluation of the intensity of the mucosal peri-oral lesions by the ROMPIS scale. If several lesions co-exist, the lesion with the most severe grade will be retained.
- Number of patients with at least one peri-oral lesion per 1000 ventilation days
- Maximum number of lesions per day

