## Follow-up

During the two recruitment periods, a logbook will be given to the paramedical staff and will include the follow-up of each change of fixation made during their stay in the ICU.

The notebook will also record the presence of vasopressors, prone positioning, extubation or re-intubation, or the presence of sedation, which are risk factors for injury in resuscitation patients.

The nurse in charge of the patient will have to change the fixation system at least once a day and if necessary during the day in case of soiling or examinations.

Duoderm-type dressings used to prevent pressure sores under the endotracheal tube will not be accepted, since this is the subject of the study. However, it can be applied as a curative measure if a lesion appears.

A verification of the correct positioning of the endotracheal tube thanks to the graduated marker will be systematically carried out once a day. If a repositioning is necessary the nurse will note the number of centimeters (either at the bottom or at the top). The mobilization of the tube (change of side) will be performed according to the usual practices of the service.

The number of mobilizations, interventions (e.g., retying the knot) on the fixation system and the number of fixation system changes will be recorded daily.

The presence or absence of lesions will be assessed daily by the nurse in charge of the patient. She will also assess the type of lesion: cutaneous or mucous and depending on the type will use the appropriate scale to assess the grade: NPUAP scale (cutaneous) or / and the ROMPIS scale (mucous).

Two photos (one with the lower lip visible and one with the upper lip visible) will be taken every day by the nurses from the day of the first fixation change = D0 until D10. In no case will the whole face of the patient be taken. The patient will not be identifiable. The photos will be taken without the fixation visible to allow the blind to be kept for the committee that will evaluate the photos. The photos will be identified only by the patient's number and the date.

Each expert will have to record the presence or not of a peri-oral lesion between D0 and D10 of maintenance of respiratory assistance via an endotracheal tube. .

For the primary endpoint, we selected a daily photo assessment until D10. The choice of this time frame was based on:

- the time of appearance of peri-oral lesions (more than 50% of them appear during the first 5 days) (7)

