#### Secondary criteria

The number of self-extubations, repositioning of the ETT will be estimated and compared using a Poisson regression model taking into account the study design. An offset of the logarithm of the intubation time will be included in the model.

The time to the first peri-oral lesion will be estimated using a random-effects survival model to account for the study design.

The time to onset will be calculated from the date of intubation to the date of first lesion onset. Patients for whom no lesion appeared will be censored at the date of extubation or at the date of discharge from intensive care or at D28. Patients who died will be censored at their date of death.

The grade of skin lesions (NPUAP scale) and mucosal lesions (Rompis scale) will be collected for each lesion. If the patient has no lesions, a grade=0 on the corresponding scale will be retained. If a patient presents several lesions, the maximum grade observed will be retained.

An ordinal logistic regression model controlling for intubation time and study design will be applied to compare both types of fixation.

The incidence of peri-oral lesions (expressed per 1000 ventilator days) will be calculated and described in each group: number of patients with at least one lesion / total number of ventilator days (up to 1ère lesions in patients with one lesion)

The maximum number of injuries per day will be estimated and compared using a linear model taking into account the study design.

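### The blinded committee records no lesion day, so time to first lesion and the lesion incidence rate have no blinded onset date within D0–D10

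*Protocol*

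**What the plan says.** Section 4.3 (Follow-up) has nurses photograph the mouth daily, "from the day of the first fixation change = D0 until D10". On labelling it says "The photos will be identified only by the patient's number and the date". The reader's task is given in the same place: "Each expert will have to record the presence or not of a peri-oral lesion between D0 and D10".

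Section 4.5.1 (Adjudication Committee) sends whole-patient files: "Each file (including all the photos of the same patient) will be randomly transmitted to each member of the adjudication committee". If the members disagree, they meet and "decide together whether or not the lesion is present".

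Section 4.6 sets out the source data. Lesion grades on the two scales appear under the daily items. The committee's output is listed separately, as "Data related to photo adjudication: presence or absence of peri-oral lesions".

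Two secondary endpoints need a date:

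- Section 2.2.2 lists "Time to the first peri-oral lesion from the time the patient is intubated until extubation", and section 6.2.1 (Secondary criteria) adds "The time to onset will be calculated from the date of intubation to the date of first lesion onset".
- Section 6.2.1 defines the incidence as patients with a lesion divided by ventilator days, counting days only up to the first lesion in those who have one.

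Section 4.1 describes the study as open. Section 4.3 has the nurse caring for the patient assess lesions every day, and the schedule carries that survey to D28. Section 2.2.1 names nurses as assessors for the two lesion-intensity objectives, but names nobody for time to first lesion or for incidence.

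**The concern.** The photo committee exists because bedside staff cannot be blinded to the device. It protects the yes/no primary endpoint. It does not protect the two endpoints that depend on when a lesion first appeared, because the committee is never asked for a day. A nurse who expects one device to cause more lesions may record them sooner or more readily in that arm, and such a tendency would pass straight into the survival model and the incidence rate.

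Two unlinked records of the same event can also disagree within D0–D10. A patient judged positive by the committee and negative by the nurse is a primary event with no onset date. The reverse patient would be an event in a nurse-dated time analysis but not in the primary analysis. This is a question of data capture, so a statistical analysis plan alone cannot settle it: it can choose between records, but it cannot supply a blinded date that nobody wrote down.

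**Working it through.** **1. The plan's own figure.** Inputs from section 6.2.2: 35% and 20%, 90% power, 5% alpha (taken as two-sided), intra-class correlation 0.1, inter-class correlation 0.05, 16 centers, two periods.

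- Patients per arm without clustering (unpooled variance): 10.507 × (0.35 × 0.65 + 0.20 × 0.80) / 0.15² = 10.507 × 0.3875 / 0.0225, rounded up to 181.
- Inflation for m patients per center-period: 1 + (m − 1) × 0.1 − m × 0.05. At m = 24 this is 1 + 2.3 − 1.2 = 2.1.
- Solving 16m = 181 × inflation: m = 181 × 0.9 / (16 − 181 × 0.05) = 162.9 / 6.95 = 23.4, rounded up to 24.
- Total: 16 × 2 × 24 = 768, as stated.

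This calculation uses only the yes/no endpoint, so the present point does not touch it.

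**2. What each record contains.**

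- *Committee (4.3, 4.5.1, 4.6):* blinded; covers D0–D10; sees every dated photo; returns one presence/absence ruling per patient; no day is requested.
- *Bedside nurse (4.3 and schedule):* not blinded; covers D0 to extubation, ICU discharge or D28; returns a dated daily assessment.

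**3. What each endpoint needs.**

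- *Primary (2.1.2):* status over the first ten days. The committee record is sufficient.
- *Time to first lesion (2.2.2, 6.2.1):* an onset date. Only the nurse record has one.
- *Incidence (6.2.1):* the numerator needs status, and the denominator needs the date of the first lesion. Again only the nurse record has a date.

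**4. Is there a rule for conflict?** Section 6.2.5 substitutes the nurse's assessment when the expert assessment is missing. It does not cover disagreement between the two. Section 6.2.1 censors patients in whom no lesion appeared, without saying by whose judgement.

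**5. How many events lack a blinded day.** Per arm 768 / 2 = 384. Expected primary events: 384 × 0.35 = 134.4 with cord and 384 × 0.20 = 76.8 with tape, together about 211. All fall within the photo window by definition, and none would have an adjudicated day.

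**6. Would blinded dating reach enough events?** Section 4.3 says that more than half of lesions appear in the first five days. On that account most first lesions would fall within the D0–D10 photos.

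**The case against.** The strongest reply is that the protocol does not say nurses date these endpoints; it names no assessor, and the choice of record could be left to the analysis plan. That is right about the wording, and nurse dating is an inference here. It rests on the absence of any other dated lesion record. Sections 4.3, 4.5.1 and 4.6 all describe the committee's output as presence or absence.

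Nurse dating also has merits, and these stand. Only the nurse covers the full horizon to D28. Stage I of the skin scale in section 4.5.1 includes temperature, tissue consistency and pain, which a photo cannot show, so the bedside date may be the earlier one. This is a reason to keep the nurse-dated analysis and put a blinded one beside it.

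A reader might infer more than the documents support:

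- *That the blinded date is lost.* The photos are dated, so it can be recovered by re-reading while the files are kept.
- *That every mismatch with the primary endpoint comes from this gap.* The primary covers ten days and the time endpoint up to 28, so a first lesion after D10 counts only in the latter, whoever reads it.
- *That the size of the conflict is known.* Disagreement in 5–15% of patients would give 38–115 of 768, but that is an assumption multiplied out; the protocol gives no agreement figure.
- *That committee-positive, nurse-negative patients are censored.* Section 6.2.1 does not say so.

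**Conclusion.** The point holds as a gap in data capture for two secondary endpoints. As the protocol is written, time to first lesion and the incidence rate have no blinded dating within D0–D10, and their event status can conflict with the adjudicated primary endpoint with no rule to resolve it. About 211 expected primary events would lack a blinded onset day, given the planned 35% and 20% and 384 patients per arm. No bias in a hazard ratio or a rate can be estimated from the documents.

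The conclusion assumes that the adjudication form collects what sections 4.3, 4.5.1 and 4.6 describe and nothing more. The weight is moderate: both endpoints are secondary, and the incidence is to be calculated and described. The gap leaves the primary endpoint and the 768 patients as they are. It would be wrong to conclude that a D10 version should replace the D28 one, since that would redefine a stated secondary endpoint.

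**What to change.** In sections 4.3, 4.5.1 and 4.6, have each expert record, besides yes or no, the first study day on which a photo shows a lesion. The date on the photo links that day to the date of intubation. Add a rule for files with a unanimous yes but different days, for example the median day with no extra meeting. The disagreement rule in section 4.5.1 implies three readers, for whom the median is a single recorded day; if a file has four, specify the earlier of the two middle days. For files that go to a meeting, the meeting records the day with its ruling.

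In section 6.2.1, keep time to first lesion and incidence to extubation or D28, and state that they are nurse-dated. Add a blinded version of each that uses the adjudicated status and day, with follow-up cut at D10.

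The cost is slightly more reading time per positive file, one short rule and one more analysis. No photo, reader or visit is added, and N and alpha do not change. Files already adjudicated can be re-read if the photos are kept. First lesions after D10 stay nurse-dated, and the report should say so.

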#### **4.7. RULES FOR TERMINATING A PERSON'S PARTICIPATION**

##### **4.7.1. Criteria for premature termination of an individual's participation in research**

An individual's participation may be terminated prematurely for the following reasons:

- Withdrawal of consent by the patient

Subjects will be able to withdraw their consent and ask to leave the study at any time for any reason.

- Transfer to another intensive care unit

##### **4.7.2. Monitoring procedures and data collection schedule**

In case of withdrawal of consent by the patient, and without prejudice to the patient's right; the data already collected will be analyzed unless the patient objects.

No other examinations specifically provided for in the protocol will be performed and no data will be used in accordance with the patient's wishes after withdrawal of consent.

The discharge of a patient from the study will not change the patient's usual management of his or her pathology.

#### **4.7.3. Discontinuation of part or all of the research at the sponsor's discretion (excluding biostatistical considerations)**

Part or the whole study may be stopped permanently or temporarily by decision of the ANSM, the CPP, or the Study Sponsor.

In all cases:

- A written confirmation will be sent to the coordinating investigator of the study (specifying the reasons for premature termination) as well as to the principal investigator of each center if applicable.

## 5. SAFETY ASSESSMENT

This protocol is subject to an update of the Safety paragraph in accordance with European Regulation n°2017/745 of the European Parliament and of the Council of 5 April 2017 concerning medical devices (MDR) and the ANSM's Notice to Sponsors (*Clinical Investigations of MD, Part IV, Vigilance*). The vigilance of this study therefore follows the provisions of **Articles 87 to 90 of the MDR (Material Vigilance)** for any incident involving the MD and **Article 80 only for adverse events related to the investigation procedure.**

### 5.1. DEFINITIONS

According to the MDR, Medical Device Coordination Group (MDCG) 2020-10/1, ANSM Notice to Sponsors (*Clinical Investigations of MDs, Part IV, Vigilance*) and NF EN ISO 14155 Clinical Investigation of MDs for Human Subjects-Good Clinical Practice:

|                                                            |                                                                                                                                                                                                                                                                                                                                                                                                                                                                                                                                                                                                                 |
|------------------------------------------------------------|-----------------------------------------------------------------------------------------------------------------------------------------------------------------------------------------------------------------------------------------------------------------------------------------------------------------------------------------------------------------------------------------------------------------------------------------------------------------------------------------------------------------------------------------------------------------------------------------------------------------|
| Adverse Events (AEs)
MDR, Article 2 (57)         | Any harmful event, unintended illness or injury, or untoward clinical sign, including an abnormal laboratory result, in participants, users, or others in a clinical investigation, whether or not related to the device under clinical investigation.

Notes (NF EN ISO 14155): This definition includes events related to the medical device under investigation or the comparator.
This definition includes the events related to the procedures involved.
For users or other persons, the definition refers only to events related to the use of the device under investigation or comparators. |
| Serious adverse events (SAE)
MDR, Article 2 (58) | Any adverse event that resulted in:

a) death;

b) a serious deterioration of the participant's health condition, which causes : 
 
- a life-threatening illness or injury;
 
- a permanent impairment of an anatomical structure or function;
 
- hospitalization or prolongation of the patient's hospitalization ;
 
- medical or surgical intervention to prevent illness or injury that endangers
 
                                                                                                                          |

the patient's life or any permanent impairment of an anatomical structure or function;

- of a chronic disease;

(c) fetal suffering, fetal death, congenital physical or mental impairment or congenital malformation.

Note (Standard NF EN ISO 14155): A procedure required by the clinical investigation plan, without serious deterioration of health, is not considered as an event serious adverse event.

